## Abstract

**Background:**

Onset of alcohol use by 14 relative to 21 years of age strongly predicts elevated risk for severe alcohol use problems, with 27% versus 4% of individuals exhibiting alcohol dependence within 10 years of onset. What remains unclear is whether this early alcohol use (i) is a marker for later problems, reflected as a pre-existing developmental predisposition, (ii) causes global neural atrophy or (iii) specifically disturbs neuro-maturational processes implicated in addiction, such as executive functions or reward processing. Since our group has demonstrated that a novel intervention program targeting personality traits associated with adolescent alcohol use can prevent the uptake of drinking and binge drinking by 40 to 60%, a crucial question is whether prevention of early onset alcohol misuse will protect adolescent neurodevelopment and which domains of neurodevelopment can be protected.

**Methods:**

A subsample of 120 youth at high risk for substance misuse and 30 low-risk youth will be recruited from the Co-Venture trial (Montreal, Canada) to take part in this 5-year follow-up neuroimaging study. The Co-Venture trial is a community-based cluster-randomised trial evaluating the effectiveness of school-based personality-targeted interventions on substance use and cognitive outcomes involving approximately 3800 Grade 7 youths. Half of the 120 high-risk participants will have received the preventative intervention program. Cognitive tasks and structural and functional neuroimaging scans will be conducted at baseline, and at 24- and 48-month follow-up. Two functional paradigms will be used: the Stop-Signal Task to measure motor inhibitory control and a modified version of the Monetary Incentive Delay Task to evaluate reward processing.

**Discussion:**

The expected results should help identify biological vulnerability factors, and quantify the consequences of early alcohol abuse as well as the benefits of early intervention using brain metrics.

## Background

Harmful alcohol use begins in adolescence, a period characterized by developments in cognition, behavior and brain maturation. Onset of alcohol use by 14 relative to 21 years of age strongly predicts elevated risk for severe alcohol use problems, with 27% versus 4% of individuals exhibiting alcohol dependence within 10 years of onset [1]. The reasons for this increased vulnerability to alcohol effects in youth need to be clarified.

Important maturational changes in brain anatomy, connectivity, and function continue well into late adolescence. Longitudinal empirical evidence suggests that brain maturation in both grey and white matter follows a postero-anterior trajectory across the cortex [2–4], where frontal areas, and white matter tracts that originate there, mature in parallel with higher order executive functional changes in later adolescence (e.g., inhibitory performance [5] or working memory [6]), relative to other, more basic cognitive functions (e.g., attention). On a functional basis, there is preliminary evidence for the dual system model [7, 8], in which top-down cognitive control networks develop linearly with age between childhood and adulthood [9, 10], while the reward sensitivity system (striatum, medial and orbital prefrontal cortices) follows a non-linear maturation that eventually caps by mid-adolescence [11].

When looking at the effects of alcohol misuse on brain maturation, neuropsychological studies in youth suggest that early alcohol abuse correlates with cognitive impairments in verbal, non-verbal and spatial working memory tasks, as well as attention and executive functions [12–14]. At the brain level, an association was found between smaller hippocampal volumes and early onset of alcohol dependence in adolescence, possibly accounting for the memory deficits noted above [15]. Moreover, functional neuroimaging studies have detected abnormal brain activations in adolescents with an alcohol use disorder, relative to healthy volunteers, when they were tested during spatial working memory tasks even though task performance did not differ [16, 17]. These findings suggest that the combination of neuroimaging with cognitive measures might be needed to capture the subtle developmental effects of adolescent onset alcohol misuse, which might translate to future addiction.

### Neurodevelopmental profiles of at-risk youth for alcoholism

#### Impulsivity (IMP)

Two major risk factors for adolescent onset of alcohol misuse are a family history of alcoholism and disinhibited psychopathology, both of which are characterized by a failure of self-control [18]. Various higher order cognitive functions that also involve inhibitory control, such as working memory and delay discounting, as well as their mediating fronto-striatal (inhibition), fronto-parietal (working memory) and striato-limbic (reward sensitivity) neural networks, are abnormal in children with disinhibited personalities and childhood disorders of impulsiveness [19–23]. Our team recently reported that IMP in 14-year olds is inversely associated with grey matter volume in the orbitofrontal cortex [24] and reduced activity within bilateral frontal brain regions during failed inhibition [25]. Furthermore, IMP and brain-related measures during failures of inhibition were prospectively predictive of substance misuse and disinhibited psychopathology over a two-year period in adolescence. Finally, there is some preliminary evidence for an interaction effect, suggesting that individuals prone to alcohol dependence, due to family history of alcoholism, are particularly susceptible to the effects of alcohol on global cognitive function [26].

#### Sensation seeking (SS)

The desire for intense and novel experiences, or SS [27], is associated with risk-taking and reckless behavior among youth [28], with heavier drinking [29, 30] and with risk for adverse drinking consequences [31]. We recently reported that SS is associated with a pattern of responding to cognitive/motivational tasks that involves a sensitivity to reward that is predictive of binge drinking over and above the contribution of co-occurring conduct problems [32]. SS and IMP appear to differentiate adolescent substance use behavior: SS is associated with early onset use, binge drinking and drug experimentation, but IMP is associated with higher quantity of use after substance use onset [33]. At the neurobiological level, we also showed that these clinical profiles could be dissociated using brain activation patterns during failed response inhibition (IMP) vs. response to reward anticipation (SS) [25]. Existing neuroimaging studies with high-risk adolescents are, for the most part, cross-sectional, so it remains unclear whether the structural and functional deficits attributed to the effects of alcohol misuse exist in individuals at risk for alcoholism prior to the onset of alcohol misuse or if early onset use causes the development of new deficits over and above existing neurocognitive abnormalities, or in interaction with such abnormalities.

### The Preventure Programme

The Preventure Programme is a school-based alcohol prevention programme targeting four specific personality risk factors for adolescent alcohol misuse: impulsivity, sensation seeking, hopelessness and anxiety sensitivity [34, 35]. The Substance Use Risk Profile Scale (SURPS) [36] has been developed by our team to enable us to identify high-risk youth based on these personality risk dimensions [29, 37]. The intervention programme, based on a cognitive-behavioral model, involves delivering two 90-min group sessions to adolescents who screen positive on one of these four personality traits in school screening. Five randomized controlled trials with high school students revealed that personality-targeted interventions reduce rates of drinking and binge drinking by up to 50% [34, 38, 39], and these effects have been shown to last up to 3 years [35, 40, 41]. Despite these very promising findings, these outcomes may underestimate the true benefits of early intervention as our previous evaluations did not assess brain function and maturation.

## Methods

### Objectives and hypotheses

In 2011, the Co-Venture Trial was funded by the Canadian Institutes of Health Research (CIHR) to test the 4-year impact of the Preventure programme on delaying early onset drinking and binge drinking in students as well as long-term addiction outcomes. A subsequent CIHR grant was awarded for the Neuroventure study, allowing us to add longitudinal neuroimaging measures to test the following objectives/hypotheses:Compare high-risk (IMP and SS) and low-risk youth on measures of brain structure and function to quantify neurocognitive endophenotypes of these two risk profiles prior to exposure to alcohol in adolescence. We expect to observe impaired fronto-striatal connectivity and function during response inhibition in IMP as well as altered function of frontal and sub-cortical regions (i.e., basal ganglia and ventral striatum) during reward anticipation in SS.Measure the correlates of adolescent drinking and binge drinking on the development of brain structure and function in adolescence, controlling for baseline differences in personality, cognitive profiles, and neural measures that are implicated in the predisposition to early onset alcohol misuse. By comparing youth who take up drinking to those who do not (regardless of intervention status), we will test the extent to which binge drinking trajectories are associated with delayed or altered development of fronto-striatal and fronto-limbic networks that mediate response inhibition and anticipation of reward/punishment. Three hypotheses will be examined. i) Global effects: abnormalities will be observed systematically across all measures of brain function and structure, ii) Developmental specificity: alcohol-induced abnormalities will be specific to regions and cognitive processes that are maturing in adolescence, and iii) Interaction effect: alcohol will exacerbate the abnormalities shown to characterize each high-risk group at baseline.Test causal hypotheses by testing whether delaying drinking (through the Preventure Programme) can produce observable protective effects on structural and functional brain development. By comparing high-risk youth who received intervention to those who did not, we will estimate an intervention effect on structural and functional brain outcomes, which again might be expressed globally across the brain, or more specifically in those areas developing during adolescence or most abnormal in high-risk groups (as revealed in objective 1).

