### Neuroventure: neuroimaging add-on study

#### Participants

Neuroventure will focus on high-risk students with SS and IMP personality profiles as they contribute most to the prediction of early onset substance-related behaviors in adolescence [42]. Thus, a subsample from the Co-Venture Trial of 60 high SS (30 of whom will receive the intervention), 60 high IMP (30 of whom will receive the intervention) and 30 low-risk (low SS and low IMP will not be invited to participate in the interventions) Grade 7 students (50% girls) will be invited to participate in this neuroimaging study (Please refer to Fig. 1 for the consort diagram and to Fig. 2 for the actual recruitment data). An independent informed consent from parents and adolescents will be obtained for the present study. Exclusion criteria will include major neuro-developmental disorders (e.g., autism), uncorrectable visual impairment or hearing deficits, severe mental health problems (e.g., schizophrenia, bipolar disorder), uninterruptable central nervous system medication, and any magnetic resonance imaging (MRI) contraindications (e.g., pregnancy, braces, etc.).

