#### Statistical analyses

The main objectives of the statistical analyses will be to characterize differences for fMRI, cortical thickness, VBM, DWI and behavioral measures between high (SS and IMP) and low-risk youth, binge drinkers and non-drinker trajectory, and those assigned to the intervention or not (with and without exposure to alcohol) over time. Two- and three-way repeated measures analyses of covariance (ANCOVA) will be performed based on region of interest (ROI) scores with covariates such as age, socioeconomic status, pubertal stage, IQ, and other drug use. For cortical thickness and VBM only a-priori defined ROI will be used (i.e., prefrontal lobes, basal ganglia, limbic brain regions and corpus callosum), as previous studies have shown that alcohol affects these regions. For fMRI, we will conduct both exploratory and ROI analyses, and for the DWI data, the regions showing linear age trends in the fMRI analysis will be used as start/finish points for probabilistic tractography.

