The main strengths of the study are that (i) the selection, intervention and measurement models are highly time-sensitive, capturing critical periods (12–14 and 14–16 years of age) when personality endophenotypes translate to risk for binge drinking and when early intervention can produce preventative effects. Furthermore, (ii) this critical period appears to overlap with the age at which drinking onset is highly related to future drinking [73], and when important brain maturation occurs [10]. In addition, (iii) this research design is highly powered as our screening procedure, which is largely based on personality assessment at 12–13 years of age, identifies individuals, SS and IMP youth, for whom binge drinking is almost certain to develop within the next 12 months. Our previous research has shown that at 13 years of age, high SS and IMP adolescents have normal rates of drinking and binge drinking (around 40%), but experience a rapid rate of onset of binge drinking between 14 and 15 years of age, with approximately 95% reporting binge drinking at 15 years of age [34]. We will also be able to (iv) test critical questions on the causal pathway from premorbid risk markers to early onset drinking, disruptions in brain function and, in turn, addiction outcomes. Finally, by being embedded into a larger population-based 5-year longitudinal randomized controlled trial, we will be able to directly (v) test the generalizability of our sample and findings to the general population, which is unique for pediatric neuroimaging studies, which tend to involve highly selective clinical samples or families with high education and socio-economic characteristics.

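### Objective 2 pools the arms in its drinker contrast without naming arm as a term, although on the protocol's figures most high-risk non-bingers would be treated

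*Protocol article*

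**What the plan says.** Under Objectives and hypotheses, the second objective rests on this contrast: "By comparing youth who take up drinking to those who do not (regardless of intervention status". The sentence before it promises an analysis "controlling for baseline differences in personality, cognitive profiles, and neural measures". All of these are baseline quantities, and arm is not among them.

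Statistical analyses lists three comparisons: high- against low-risk youths, "binge drinkers and non-drinker trajectory", and "those assigned to the intervention or not (with and without exposure to alcohol) over time". The method is two- and three-way repeated-measures ANCOVA on region-of-interest scores "with covariates such as age, socioeconomic status, pubertal stage, IQ, and other drug use". That list is open, and it does not name arm.

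Participants gives the design: "60 high SS (30 of whom will receive the intervention), 60 high IMP (30 of whom will receive the intervention", plus "30 low-risk (low SS and low IMP will not be invited to participate in the interventions". That is 60 treated and 60 untreated high-risk youths and 30 untreated low-risk youths. For high sensation-seeking and impulsive youths, the Discussion cites earlier research with "approximately 95% reporting binge drinking at 15 years of age". The Abstract credits the programme with a 40-60% reduction in uptake of drinking and bingeing. The section on the Preventure Programme puts the reduction at no more than 50%, lasting up to 3 years.

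**The concern.** The programme exists to change drinking. If it works as described, arm and drinking status will be strongly associated among high-risk youths. A contrast that pools the arms and omits arm then credits alcohol with whatever the programme does to the brain by other routes.

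Such routes are plausible on the protocol's own account. The programme is cognitive-behavioural and targets impulsivity and sensation seeking, and the Background links those traits to the inhibition and reward networks that Objective 2 measures. Adjusting for baseline personality, cognition and brain measures cannot remove an effect that arises after baseline. What is at stake is whether an Objective 2 result can be read as being about alcohol.

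**Working it through.** The protocol states no expected number of drinkers or non-drinkers, so there is no figure of its own to reproduce. The check builds one from its inputs, for bingeing in high-risk youths at about age 15, before attrition.

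**Inputs.** 60 treated and 60 untreated high-risk youths (Participants). Binge rate 0.95 at age 15 (Discussion), assumed to be the untreated rate. Reduction r = 0.40 to 0.60 (Abstract), assumed first to be a relative reduction in the proportion bingeing.

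**Non-bingers.**
- Untreated: 60 × (1 − 0.95) = 3.
- Treated: 60 × (1 − 0.95 × (1 − r)). This is 60 × (1 − 0.57) = 25.8 at r = 0.40 and 60 × (1 − 0.38) = 37.2 at r = 0.60.

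**Treated share of non-bingers.** 25.8/28.8 = 89.6% and 37.2/40.2 = 92.5%. At r = 0.50 it is 31.5/34.5 = 91.3%.

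**Treated share of bingers.** 34.2/(57 + 34.2) = 37.5% and 22.8/(57 + 22.8) = 28.6%.

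**Carry-over.** With no adjustment for arm, a direct programme effect of D standard deviations enters the high-risk contrast as D × (treated share of non-bingers − treated share of bingers). The protocol gives no D. With D = 0.3 assumed: 0.3 × (0.896 − 0.375) = 0.16 SD and 0.3 × (0.925 − 0.286) = 0.19 SD. The result is proportional to D: 0.05-0.06 SD for D = 0.1 and 0.26-0.32 SD for D = 0.5.

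**Other readings of the 40-60%.**
- *New uptake only.* The Discussion gives about 40% at age 13, so 55 percentage points are new by 15. Treated non-bingers are 60 × (1 − 0.40 − 0.55 × (1 − r)) = 16.2 to 22.8.
- *Odds scale.* The untreated odds are 0.95/0.05 = 19. Multiplied by (1 − r), they give treated binge rates of 91.9% to 88.4%, so 4.8 to 7.0 non-bingers.

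| Reading | Treated share, non-bingers | Treated share, bingers | Carry-over at D = 0.3 |
|---|---|---|---|
| Relative risk | 90-93% | 29-38% | 0.16-0.19 SD |
| New uptake only | 84-88% | 39-43% | 0.12-0.15 SD |
| Odds | 62-70% | 48-49% | 0.04-0.07 SD |

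**Sensitivity on the relative-risk reading.** With a 95% untreated rate, a 20% reduction gives a treated share of non-bingers of 82.8%, and a 10% reduction gives 74.4%. With a 50% reduction, untreated rates of 90%, 80% and 60% give 84.6%, 75.0% and 63.6%.

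**All 150 youths.** The low-risk binge rate is not given. Assumed rates of 0%, 40% and 80% put the treated share of all non-bingers at 44-53%, 55-64% and 74-81%. Untreated high-risk youths are at most about 9% of all non-bingers in these cases.

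**Can arm and bingeing be separated?** The phi correlation in high-risk youths is (25.8 × 57 − 3 × 34.2)/√(28.8 × 91.2 × 60 × 60) = 0.445 at r = 0.40, and 0.604 at r = 0.60. VIF = 1/(1 − phi²) = 1.25 to 1.57. The standard error of the drinking effect grows by √1.25 = 1.12 to √1.57 = 1.25, so separation is feasible.

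**The case against.** No Objective 2 model is written out. The phrase about intervention status says who is compared, not that arm is left out of the model. The covariate list is open, a full analysis plan may name arm, and Statistical analyses does set arm beside alcohol exposure in one comparison. This has some weight: arm is not excluded. But that comparison is the arm contrast; nothing there carries arm into the drinker contrast. The one thing the article does fix for Objective 2 is pooling across arms.

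Arm also distorts the contrast only if the programme reaches the brain other than through drinking. That is right, and the protocol neither shows nor rules out such a route. The 90-93% further depends on the relative-risk reading and on taking 95% as the untreated rate.

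A reader might infer three stronger points that the documents do not support:
- *Drinking is also left confounded with risk group.* Objective 2 promises control for baseline personality, which defines risk group, and no low-risk binge rate is given to size any imbalance.
- *The trajectory groups mislabel scans taken before drinking began.* The text does not say how the groups are formed or used. In a group-by-time analysis, a later drinker's first scan is the pre-exposure baseline that the test needs.
- *The near-certain onset of bingeing, listed as a strength, contradicts Objective 2.* The Discussion does not tie that claim to this objective, and the figures above still leave 29-40 high-risk non-bingers plus low-risk youths.

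**Conclusion.** The point holds in a limited form. As written, Objective 2 pools the arms and names no adjustment for arm. On the protocol's own figures, drinking status and arm would be closely linked among high-risk youths, with about 3 untreated against 26-37 treated non-bingers. A direct programme effect of 0.3 SD, which is an assumed value, would add about 0.16-0.19 SD to the high-risk drinker contrast, or less on the new-uptake and odds readings.

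The shares concern bingeing, in high-risk youths, at about age 15. They do not describe any drinking, the whole sample of 150, or the 48-month scan, since programme effects are stated to last up to 3 years. It would be wrong to say that about 90% of Objective 2's whole comparison group is treated: that share cannot be computed from the document.

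**What to change.** State in the Objective 2 analysis that the model includes intervention arm and arm-by-time, and keep the promised baseline personality term as personality group. Low-risk youths are all untreated, so once personality group is in the model the arm term is estimated from the high-risk youths. Tabulate drinkers and non-drinkers by arm and risk group. Report the drinking contrast within each arm as a sensitivity analysis, and say in advance that the untreated high-risk non-drinker cell is expected to be very small (about 3 on the binge figures), so that the untreated-arm result will be imprecise for high-risk youths.

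This changes analysis wording only and needs no new data. The cost is a few degrees of freedom and an interval for the drinking effect that is about 12-25% wider in high-risk youths (VIF 1.25-1.57). The drinking groups themselves need not be replaced by another exposure measure to meet this point.

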
### The Co-Venture Trial (from which the participants are recruited)

This study uses a cluster-randomized controlled design in which 31 schools (cluster) agreed to conduct annual surveys for 5 years with all consenting adolescents (*N* = 3826) who were enrolled in Grade 7 in September 2012. Schools were randomly assigned to i) be trained and assisted in the delivery of the Preventure programme to Grade 7 high-risk adolescents or ii) not be exposed to the intervention. Adolescents were screened using the SURPS [36] during their Grade 7 year and invited to participate in personality-specific Preventure workshops if they scored one standard deviation above the school mean on one of the four SURPS dimensions. The Co-Venture clinical Trial is registered on www.ClinicalTrials.gov, “Co-Venture: a Cluster Randomized Trial Investigating the Effects of Selective Intervention on Adolescent Cognitive Development and Addiction”, study NCT01655615.

